### Measures

2.9

#### Screening measure

2.9.1

##### Sociodemographic and clinical history questionnaire

2.9.1.1

The Sociodemographic and Clinical History Questionnaire is an instrument developed to be used as a screening measure for an online CBT intervention (Richards et al., 2013). It includes questions such as alcohol or drug misuse, suicidal thoughts, confidence in using the internet. It also measures whether they have a diagnosis of an organic mental health condition (i.e., schizophrenia, psychosis, and bipolar disorder) and whether they previously received psychotherapy for depression or anxiety. The questionnaire is adapted for the present study with additional health-related questions such as diagnosis of breast cancer, length of time since the diagnosis, received medical treatments (chemotherapy, radiotherapy, or hormonal therapy), and main carer related questions such as whether they have someone who supports them.

#### Primary outcome measure

2.9.2

##### Hospital anxiety and depression scale (HADS)

2.9.2.1

HADS is a 14-item self-report questionnaire, which is designed to measure anxiety and depression symptoms in medical settings (Zigmond and Snaith, 1983) will be used as a primary outcome measure. It consists of two 7 item subscales: depression (HADS-D) and anxiety (HADS-A). Each item is rated on a 4-point scale ranging from 0 “Not at all” to 3 “Most of the time”. After reverse scoring eight of the items, HADS-D and HADS-A subscale totals can be summed, giving a maximum score of 21 for each subscale. The HADS-T is the total score of depression and anxiety subscales, which will be used in the present study. High scores represent higher psychological distress. The HADS-T was chosen over other depression and anxiety measures as it measures anxiety and depression without relying on somatic symptoms such as fatigue or insomnia, which are experienced by cancer survivors as a result of their illness and/or medical treatment. The HADS is validated and extensively used in the measurement of distress among cancer survivors (Vodermaier et al., 2009; Mitchell et al., 2010).

#### Secondary outcome measures

2.9.3

##### Cancer-related quality of life (EORTC QLQ-C30)

2.9.3.1

To assess the overall health-related life quality of cancer survivors, a single item from the European Organization for Research and Treatment of Cancer Quality of Life Core Questionnaire (EORTC) will be used (Aaronson et al., 1993). It is a 30-item scale that assesses various facets of health-related quality of life; only the final item “How would you rate your overall quality of life during the past week?” will be used in the current study. Responses to this single item are rated on a 7-point scale ranging from 1 “very poor” to 7 “excellent”.

##### Breast Cancer Worry Scale (CWS)

2.9.3.2

The six-item version of the Cancer Worry Scale (CWS) (Custers et al., 2018) will be used to assess breast cancer survivors' concerns about cancer recurrence and the impact of these concerns on their daily functioning. The scale was originally to measure fear of developing cancer in women at risk of hereditary cancer (Lerman et al., 1991). The items include “How often have you thought about your chances of getting cancer again?”, “Have these thoughts affected your mood?”. All items are rated on a 4-point scale ranging from 1 “never” to 4 “almost always”, with scores ranging from 6 to 24 and higher scores indicating more frequent worries about breast cancer. The 6-item version of the CWS has good construct, convergent and divergent validity, and high internal consistency to detect fear of cancer recurrence in breast cancer survivors, with a Cronbach alpha coefficient of 0.90 (Custers et al., 2018).

##### Brief coping orientation to problems encountered (brief COPE) inventory

2.9.3.3

The Brief COPE is a 28-item measure, which assesses strategies used for coping with a stressful life event (Carver, 1997). This inventory is an abbreviated version of the full 60-item COPE Inventory (Carver et al., 1989) and assesses 14 different coping strategies: self-distraction, active coping, denial, substance use, emotional support, instrumental support, behavioural disengagement, venting, positive reframing, planning, humour, acceptance, religion, and self-blame (Carver, 1997). It has response options range from (1) I haven't been doing this at all to (4) I have been doing this a lot. It measures both adaptive and maladaptive coping strategies and is commonly used for measuring coping with health-related conditions (Rand et al., 2019). In the present study, the instructions were modified to ask how participants had been coping with breast cancer-related stress in their life. Item samples are: “I've been turning to work or other activities to take my mind off things”, “I've been concentrating my efforts on doing something about the situation I'm in”. This scale will be used to measure potential changes in survivors' ways of coping with stress related to breast cancer before and after the intervention. The Brief COPE has been demonstrated to be reasonably reliable with Cronbach alpha levels ranging from 0.50 to 0.90 for each subscale (Carver, 1997; Rand et al., 2019). In the present study, instead of 14 subscales, 2 coping dimensions that assess efforts to move toward goals (active coping) and to disengage from goal pursuits (avoidant coping) will be used (Kershaw et al., 2004; Rand et al., 2019).

##### Medical outcomes study social support survey (MOS-SSS)

2.9.3.4

Survivors' perceived support will be measured using the Medical Outcomes Study social support survey (MOS; Sherbourne and Stewart, 1991). The scale was originally developed to measure the perceived availability of functional social support among people with chronic illness. The original scale assesses four dimensions of social support: (1) emotional/informational support (the expression of positive affect, empathetic understanding, and the encouragement of expressions of feelings, and the offering of advice, information, guidance, or feedback), (2) tangible support (the provision of material aid or behavioural assistance), (3) positive social interaction (the availability of other persons to do fun things with you), and (4) affectionate support (involving expressions of love and affection). In the present study, only the emotional/informational support subscale (8 items) will be used as carer access may only influence the emotional/informational social support perceptions of survivors. Survivors will be asked how true each statement was based on the support available to them during the past 7 days. Sample items include: “if you need it, how often is someone available you can count on to listen to you when you need to talk?”, “if you need it, how often is someone available to give you good advice about a crisis?”. The responses to all items range from “none of the time” to “all of the time”; higher scores indicating better perceived social support. It had excellent reliability with 0.97 for the overall scale and subscales with a Cronbach's alpha of 0.96, 0.94, 0.91, and 0.92, respectively. This scale has been used in many studies with breast cancer patients (Chang et al., 2019; Ganz et al., 2003; Kornblith et al., 2003; Kroenke et al., 2013; Sousa Rodrigues Guedes et al., 2020).

##### Survivor-carer cancer communication

2.9.3.5

Cancer communication difficulties between survivors and carers will be measured by 6-items drawn (Family communication subscale) from the 30-item measure of Patient-Family Discord (Francis et al., 2010; Siminoff et al., 2006). This measure was chosen as the items are specific to cancer communication and expression of feelings about cancer, which were addressed during the adaptation of the iCBT intervention. Some examples of the items are: “My family does not really listen when I talk about my cancer”, “I avoid talking about cancer to my family because I don't want to upset them”. The word family was changed with the carer in the breast cancer survivors' version as this study is focusing only on the carer and survivor relationship. In the carer version of the scale, items were changed as “She does not really listen when I talk about her cancer”, “I avoid talking about cancer to her because I don't want to upset her”. The items are rated on a 5-point scale response ranging from 1 to 5 (1 = strongly agree, 5 = strongly disagree) in the present study. The scale demonstrated a reliability coefficient of 0.63 (Francis et al., 2010).

##### Survivor-carer relationship quality

2.9.3.6

Survivors and carers will be asked to rate the quality of their relationship with each other on a scale ranging between 0 and 10. A score of 10 represents the excellent quality of relationship and 0 represents the very poor quality of the relationship. This single item scale measuring the relationship quality between survivors and carers will allow them to base their judgments on aspects of their relationship that are most important for them (based on Cantril, 1965; Kuijer et al., 2004; Rottmann et al., 2015).

#### Other measures

2.9.4

##### Helpful aspects of therapy form (HAT)

2.9.4.1

The HAT assesses the most helpful and hindering effects for survivors during the therapy (Burke et al., 2019; Llewelyn, 1988). It asks survivors to describe, in their own words, what was most helpful and what was least helpful in each module for them. It can be anything that participants, the module, or supporters said or did. To clarify their associated impacts, the scale also asks them to describe what made the event helpful or hindering for them.

##### Satisfaction with online treatment (SAT)

2.9.4.2

The SAT assesses satisfaction with online treatment (Richards and Timulak, 2013). The first part consists of questions about the use of the computer to access treatment, how easy it was for them to use online treatment, whether the treatment they received would have a lasting effect on them, and whether they would specifically recommend online treatment to others. Responses are reported on a scale ranging from “Agree very strongly” to “Disagree very strongly”. The second part consists of two qualitative questions asking participants to describe what they most liked and least liked about the treatment.

### Planned analyses

2.10

#### Baseline comparisons

2.10.1

All data will be organised and prepared in the Statistical Package for the Social Sciences (SPSS). Demographic information and characteristics of the participants (i.e., age, education level, breast cancer stage, presence of the main carer) will be analysed using descriptive statistics. Group differences in demographic and clinical characteristics at baseline will be analysed with the Chi-squared test for categorical variables, and analysis of variance (ANOVA) or *t*-tests for continuous variables.

#### Effectiveness analyses for primary and secondary outcomes

2.10.2

Linear Mixed Modelling (LMM) will be used to compare pre-treatment, post-treatment, and 2-month follow-up scores of the survivors in three groups (iCBT alone, iCBT with the carer, and TAU control) on the main outcome measure of depression and anxiety as well as secondary outcome measures including cancer-related quality of life, coping, and fear of cancer recurrence. The intention-to-treat (ITT) and per-protocol (PP) approach will be used to test the effectiveness of the treatment groups over the TAU control group. According to the ITT approach, participants who leave the study early or do not comply with the protocol are considered as belonging to the treatment arm they were originally randomised to. On the other hand, PP analytical approach does not include patients who violate the protocol, switch the allocation arm throughout the study, do not adhere to the assigned treatment or do not undergo to the scheduled assessments over time. Thus, it helps capture the “true” exposure to treatment. As suggested, the ITT will be used as the main method of analysis to determine effectiveness as it provides an unbiased estimate to treatment effect, and the PP will be used as a secondary and supportive analysis (Tripepi et al., 2020) to provide complementary information about the iCBT intervention. Restricted maximum likelihood (REML) estimation will be used to account for missing data due to participant drop-out. Significant effects will be followed up using pairwise contrasts comparing mean pre-treatment scores to post-treatment scores. Between-group (Hedges' *g*) and within-group (Cohen's *d*) effect sizes will be calculated using the pooled standard deviation and adjusted for sample size. For Hedges' *g* and Cohen's *d* an effect size 0.20 is considered small, 0.50 moderate, and 0.80 large.

Mediation analyses using PROCESS for SPSS (Hayes, 2013; Hayes and Rockwood, 2017) will be used to test the role of change in coping strategies following the iCBT treatment on survivors' outcomes such as depression and anxiety scores and cancer-related quality of life. The estimates of indirect effects will be generated using the bootstrapping method (*n* = 5000 bootstrap re-samples) and a 95% confidence interval (Preacher and Hayes, 2008). If the 95% confidence interval does not include the value of zero, this supports a claim of mediation, i.e., the effect of the independent variable on the outcome variable is contingent upon the effect of the proposed mediator. The bootstrapping method was preferred over the Sobel test as it does not impose the assumption of normality of the sampling distribution and the sampling distribution of the indirect effect is frequently non-normal.

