### Hypotheses and research questions

1.5

Hypothesis about the primary outcomes:**H1**Survivors in both treatment groups (Group 1 and Group 2) are expected to show a greater reduction in depression and anxiety symptoms than survivors in the TAU (Group 3) at post-treatment and 2-month follow-up.

Hypotheses about the secondary outcomes:**H2**Survivors in both treatment groups (Group 1 and Group 2) are expected to have greater improvements in cancer-related quality of life, coping, and fear of recurrence compared to survivors in the TAU (Group 3) at post-treatment and 2-month follow-up.**H3**Survivors in both treatment groups (Group 1 and Group 2) are expected to use more active coping strategies than survivors in the TAU (Group 3) at post-treatment and 2-month follow-up.**H4**A reduction in depression and anxiety symptoms of survivors in both treatment groups (Group 1 and Group 2) is expected to be mediated by the change in coping strategies after controlling for depression and anxiety levels at baseline.**H5**An improvement in cancer-related quality of life in both treatment groups (Group 1 and Group 2) will be mediated by the change in coping strategies after controlling for cancer-related quality of life at baseline.

The effects of carer access will be explored using the following research questions:

**RQ1.** Is there a difference in depression and anxiety scores between iCBT alone (Group 1) and iCBT with the carer access (Group 2) at post-treatment after controlling for baseline depression and anxiety scores?

**RQ2.** Is there a difference in perceived social support between iCBT alone (Group 1) and iCBT with the carer access (Group 2) at post-treatment after controlling for baseline perceived social support?

**RQ3.** Is there a difference in survivor-carer relationship outcomes (cancer-related communication quality and relationship quality) of survivors in iCBT with carer access between baseline and post-treatment?

**RQ4.** Is there a difference in survivor-carer relationship outcomes (cancer-related communication quality and survivor-carer relationship quality) of carers between baseline and post-treatment?

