### Randomisation

2.5

Eligible participants will be randomly assigned to either iCBT intervention (n = 72) or treatment-as-usual control (*n* = 36) with a 2:1 ratio. Those who are assigned to iCBT group and have carers will be asked whether they will participate with or without their main carer. Participants will be assigned to iCBT alone or iCBT with carer access based on their preference and informed immediately about their group assignment. Survivors in the iCBT alone group (Group 1) will be using the iCBT programme by themselves, and survivors in the iCBT with the main carer access group (Group 2) will be using the same programme, but their main carers will also have access to the programme content using a separate username and password. Participants in the treatment-as-usual control group (Group 3) will continue their usual care and will not receive the iCBT programme during this study. They will fill out the same measures as the other two groups at pre-treatment, post-treatment, and 2-month follow-up.

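### The main effectiveness model compares TAU with two preference-formed iCBT groups under an ITT label; the randomised iCBT-versus-TAU contrast is never stated

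*Protocol article*

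**What the plan says.** **What is randomised.** Protocol article, section 2.5: "Eligible participants will be randomly assigned to either iCBT intervention (n = 72) or treatment-as-usual control", in a 2:1 ratio with 36 in TAU.

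**How Groups 1 and 2 arise.** Same section: "Those who are assigned to iCBT group and have carers will be asked whether they will participate with or without their main carer", and then "Participants will be assigned to iCBT alone or iCBT with carer access based on their preference". A survivor without a carer can only be in Group 1. TAU survivors are not described as being asked for a preference.

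**The main analysis.** Section 2.10.2 uses a linear mixed model to "compare pre-treatment, post-treatment, and 2-month follow-up scores of the survivors in three groups (iCBT alone, iCBT with the carer, and TAU control". Under ITT, participants who leave or do not comply "are considered as belonging to the treatment arm they were originally randomised to". ITT is the main method "as it provides an unbiased estimate to treatment effect".

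**The hypothesis.** H1 in section 1.5: "Survivors in both treatment groups (Group 1 and Group 2) are expected to show a greater reduction in depression and anxiety symptoms" than TAU. H2 and H3 name the same two groups. The sample size in section 2.4 also rests on the three-group comparison (f = 0.30).

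**The caveats.** Sections 2.1 and 2.10.3 and the Discussion acknowledge allocation by preference. They apply the exploratory label only to the effects of carer access. The Discussion calls the trial adequately powered for the primary and secondary hypotheses.

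**The concern.** The ITT definition works only for the two arms to which people are randomised. Nobody is randomised to iCBT alone or to iCBT with carer access, so the three-level factor in the confirmatory model does not match the definition given beside it.

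TAU contains both the survivors who would have chosen carer access and those who would not, or could not. Group 1 and Group 2 are each a selected part of the iCBT arm, and each is set against that unselected mixture. A significant three-group result can then reflect who chose what, with no treatment effect at all. The three-group test also spends degrees of freedom on Group 1 versus Group 2, a difference that the protocol itself regards as exploratory. What is at stake is the trial's one randomised comparison, which is the basis for any claim of effectiveness.

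**Working it through.** **1. The plan's own figures.** Attrition of 25% reproduces: 81/0.75 = 108, 54/0.75 = 72, 27/0.75 = 36. The 81 itself cannot be confirmed, because section 2.4 gives neither the correlation nor the F test used. The steps below take 81 completers (54 iCBT, 27 TAU) as given.

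**2. Which comparisons randomisation protects.**

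| Comparison | Groups formed by | Protected? |
|---|---|---|
| Groups 1+2 vs TAU | randomisation | yes |
| Group 1 vs TAU | randomisation, then carer and preference | no |
| Group 2 vs TAU | randomisation, then carer and preference | no |
| Three-group test | includes Group 1 vs Group 2 | no |

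The only follow-up contrasts in section 2.10.2 compare pre-treatment with post-treatment means. They do not restore the first row.

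**3. Possible bias for change from baseline.** Assumptions: no treatment effect; would-be Group 1 and Group 2 survivors differ by 0.3 SD in their change; pre-post correlation 0.6; a share q chooses carer access. TAU has the same mix, so Group 2 vs TAU is biased by (1 − q) × 0.3. The SD of change is √(2 × (1 − 0.6)) = 0.894.

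- Even split, 27 vs 27: bias 0.5 × 0.3 = 0.15; SE = 0.894 × √(1/27 + 1/27) = 0.243; ratio 0.62; two-sided rejection about 9%.
- q = 25%, Group 2 with 14 vs 27: bias 0.75 × 0.3 = 0.225; SE = 0.894 × √(1/14 + 1/27) = 0.295; ratio 0.76; rejection about 12%.
- If the 0.3 SD difference is constant over time, it cancels in the change score: bias 0, rejection about 5%.

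Three-group test of change in the same trajectory scenario, even split: noncentrality = (27 × 0.15² + 27 × 0.15²)/0.8 = 1.52 on 2 and 78 df, so rejection is about 17%. With 14 choosing carer access, the group shifts are −0.078 and +0.222, the noncentrality is 1.17 and rejection is about 14%. The pooled iCBT vs TAU test stays at 5%, because the two shifts cancel when weighted by group size.

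**4. Power, with the same group-by-time test in both cases.** Assumptions: both iCBT groups lower by d = 0.5 at post-treatment and follow-up, compound symmetry with correlation ρ.

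- Group weight: 54 × 27/81 = 18.
- Time profile (0, d, d), centred: sum of squares (2/3)d².
- Noncentrality: 18 × (2/3) × 0.25/(1 − ρ) = 3/(1 − ρ), the same for both tests. Only the degrees of freedom differ.

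| ρ | Noncentrality | Three groups (4, 156 df) | Two arms (2, 158 df) |
|---|---|---|---|
| 0.5 | 6.0 | 0.46 | 0.58 |
| 0.6 | 7.5 | 0.56 | 0.68 |
| 0.7 | 10.0 | 0.70 | 0.81 |

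**The case against.** **The two-arm reading is available.** The arm originally randomised to can only be iCBT or TAU, and section 2.10.2 speaks of testing the treatment groups over TAU. A three-level model also yields the randomised comparison through a contrast weighted by group size, and naming contrasts is often left to an analysis plan. This stands in part. A reader might infer that the trial cannot deliver a randomised estimate, or that its ITT result must be biased; the document does not support that, since the pooled comparison remains obtainable. But the article does more than stay silent: the hypotheses, the sample size and the model all state three groups.

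**Bias is not automatic.** H1 concerns reduction in symptoms, so a stable prognostic difference drops out. This stands, and the 9% to 12% is conditional. Section 2.10.3, however, itself allows that having a carer may go with higher initial support, and that this may influence response to the programme. It adjusts for this only in Group 1 versus Group 2.

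**H1 predicts benefit in both groups.** A reader might take 9% to 12% as the false-positive rate of H1. It is not. Selection moves the two groups in opposite directions, and the simulated chance that both falsely show benefit is below 0.5%. The rates apply to each group's contrast with TAU taken alone.

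**The power gain can be overstated.** A one-degree-of-freedom, baseline-adjusted pooled contrast reaches 0.745 under the same assumptions. Setting that against 0.56 changes the test and the adjustment as well as the grouping. Pooling alone moves 0.56 to 0.68.

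**The preference issue is already acknowledged.** It is, but only for carer-access effects, not for each group against TAU.

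**Conclusion.** The point holds. The confirmatory analysis is stated on three groups, two of them formed after randomisation, and this conflicts with the protocol's own ITT definition. The structural part rests on the text alone and needs no assumption.

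The sizes do rest on assumptions. A 0.3 SD difference in trajectory and correlation 0.6 give a type I error of about 9% to 12% for a single group-versus-TAU change contrast, and about 5% if the difference is constant over time. Pooling the randomised arms gains 11 to 12 percentage points of power at d = 0.5 over correlations 0.5 to 0.7. The document gives neither the share choosing carer access nor the link between preference and symptom course, so whether bias will occur, and how large it would be, is unknown.

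**What to change.** - In section 2.10.2, make the primary ITT analysis of HADS-T all survivors randomised to iCBT (Groups 1 and 2 together) versus TAU. Use a two-arm linear mixed model, or keep the three-level factor and name a contrast of Groups 1 and 2, weighted by their size, against TAU.
- Use the same comparison for the outcomes under H2 and H3.
- Reword H1 to H3 to refer to survivors randomised to iCBT.
- Move each preference group versus TAU to section 2.10.3, labelled exploratory and non-randomised.

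The cost is wording in sections 1.5, 2.10.2 and 2.10.3. Randomisation, recruitment and data collection do not change, and no new data are needed. The change should be fixed and dated before outcome data are analysed.

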### Sample size

2.4

The G-Power software programme was used to carry out power analysis and determine the sample size needed for three-group, pre-test, post-test, and follow-up design. The data from a randomised controlled trial of an iCBT programme for depression and anxiety among cancer survivors revealed a large within-between interaction effect size for the HADS-Total after comparing the pre-treatment and post-treatment scores of the iCBT and the TAU (Murphy et al., 2019). To calculate the sample size, we powered for the changes in the primary outcome (depression and anxiety symptoms, measured by the HADS-Total) when comparing the treatment groups (iCBT alone and iCBT with the carer access) with the TAU. Assuming a medium effect size (*f* = 0.30) for the pre, post, follow-up comparisons between iCBT alone, iCBT with carer access, and TAU with a power of 0.80 and significance level of α = 0.05, the sample size is calculated to be 27 breast cancer survivors in each group and 81 in total (54 in the iCBT group and 27 in the TAU group using 2:1 ratio). Considering the 25% attrition (Richards et al., 2018), 108 breast cancer survivors in total (*n* = 72 for iCBT and = 36 for TAU) will be recruited.

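### The only follow-up contrasts named are pre- versus post-treatment, so no stated contrast isolates the iCBT-versus-TAU difference that H1 to H3 claim, least of all at 2 months

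*Protocol article*

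**What the plan says.** **Hypothesis.** In section 1.5, H1 says that survivors in both iCBT groups "are expected to show a greater reduction in depression and anxiety symptoms than survivors in the TAU (Group 3) at post-treatment and 2-month follow-up". H2 and H3 make between-arm claims at the same two time points for the secondary outcomes.

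**Model.** Section 2.10.2 says "Linear Mixed Modelling (LMM) will be used to compare pre-treatment, post-treatment, and 2-month follow-up scores of the survivors in three groups", and that the intention-to-treat and per-protocol approaches "will be used to test the effectiveness of the treatment groups over the TAU control group".

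**Follow-up of the model.** The same section then says "Significant effects will be followed up using pairwise contrasts comparing mean pre-treatment scores to post-treatment scores". No other contrast is named for H1 to H3. Between-group and within-group effect sizes "will be calculated using the pooled standard deviation and adjusted for sample size", with no time point given.

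**Data and power.** Section 2.5 says of the TAU group: "They will fill out the same measures as the other two groups at pre-treatment, post-treatment, and 2-month follow-up". Section 2.4 powers the trial on HADS-Total "when comparing the treatment groups (iCBT alone and iCBT with the carer access) with the TAU", with an effect size assumed "for the pre, post, follow-up comparisons between iCBT alone, iCBT with carer access, and TAU".

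**The concern.** The rule for following up the model does not match the hypothesis. H1 is about a difference between arms at two times. The named contrast is a difference between two times, and the second of H1's two time points is not in it.

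Three things are at stake.

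- The 2-month claim has no contrast of its own. It would rest on an omnibus effect that does not show at which time the arms differ.
- The sentence applies to any significant effect. A significant effect of time alone, which natural recovery or regression to the mean can produce, would lead to the same pre-post contrasts. With three groups, a significant effect could also come from a difference between the two iCBT groups. Those groups are formed by preference, and their difference is not H1.
- If the within-arm changes are what gets reported, a reader may take a significant fall in iCBT beside a non-significant one in TAU as proof of benefit. It is not.

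The exploratory carer questions are better specified in this respect: RQ1 and RQ2 in section 1.5 name a between-group comparison at post-treatment with control for baseline.

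**Working it through.** **1. Inputs.** From section 2.4: 54 iCBT and 27 TAU evaluable, 81 in total, two-sided 0.05 taken for single contrasts. The attrition step reproduces: 81 / (1 − 0.25) = 108. The correlation between repeated measures (ρ) is not stated, so 0.5 to 0.7 is assumed. Changes and effects are in baseline SD units and are also assumed.

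**2. Hypothesis against contrasts.**

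| Needed for H1 to H3 | Named in section 2.10.2 |
|---|---|
| iCBT versus TAU at post-treatment | Only through the omnibus model; the named contrast is pre versus post |
| iCBT versus TAU at 2 months | Only through the omnibus model; no contrast includes 2 months |

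**3. Can the omnibus test show the 2-month effect?** Pool the iCBT groups, assume compound symmetry, and let v be the arm differences in change from baseline at post-treatment and at 2 months. The covariance of their estimates is S = (1/27 + 1/54)(1 − ρ) × [[2, 1], [1, 2]], and the noncentrality is λ = v′S⁻¹v.

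- Effect d at post-treatment only, v = (d, 0): λ = (2d²/3) / [(1 − ρ)(1/27 + 1/54)].
- Effect d at both times, v = (d, d): the same expression.

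With d = 0.6 and ρ = 0.5: λ = 0.24 / (0.5 × 0.05556) = 8.64. Power on 2 df at 0.05 (chi-square approximation) is 0.753 in both cases. The test is equally likely to be significant whether or not the effect lasts to 2 months.

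**4. What if efficacy were read from within-arm pre-post tests?** Assume no treatment effect and the same fall δ in both arms. The paired t test has noncentrality δ√n / √(2(1 − ρ)). The probability that iCBT is significant and TAU is not is P(iCBT significant) × [1 − P(TAU significant)].

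| δ | ρ | iCBT, n = 54 | TAU, n = 27 | iCBT yes, TAU no |
|---|---|---|---|---|
| 0.3 | 0.5 | 0.581 | 0.324 | 0.39 |
| 0.3 | 0.6 | 0.677 | 0.389 | 0.41 |
| 0.3 | 0.7 | 0.798 | 0.491 | 0.41 |
| 0.4 | 0.5 | 0.823 | 0.517 | 0.40 |
| 0.4 | 0.6 | 0.897 | 0.609 | 0.35 |
| 0.4 | 0.7 | 0.961 | 0.733 | 0.26 |

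The range is 26-41%. It depends on δ: at 0.6 SD it drops to 3-15%. If the iCBT groups are analysed separately and split evenly at 27 each, the figure for one iCBT group against TAU is p(1 − p), for example 0.517 × 0.483 = 0.25 at δ = 0.4 and ρ = 0.5.

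**5. What if the arm-by-time effect must be significant first?** Simulating the same null cases (40,000 runs each), the joint event of a significant between-arm test, iCBT significant and TAU not, occurs about 2.4% of the time.

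**6. Precision from baseline adjustment.** The contrast variance is proportional to 2(1 − ρ) for change scores and to 1 − ρ² with baseline as covariate. The ratio is (1 + ρ)/2 = 0.75, 0.80 and 0.85 at ρ = 0.5, 0.6 and 0.7, a reduction of 25%, 20% and 15%. At an assumed d = 0.5 with 54 versus 27, power for one contrast goes from 0.554, 0.649 and 0.772 to 0.677, 0.745 and 0.835.

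**The case against.** A reader might infer that the between-arm difference in H1 is never tested, or is left to a descriptive Hedges' g. The article does not support that. Section 2.10.2 plans a three-group, three-time model, states that its purpose is to test the treatment groups over TAU, and includes the 2-month data. Between-arm inference exists at model level. This part of the objection stands in full.

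The quoted sentence also does not say whether the pre-post contrasts are taken within each arm or compared between arms, and nowhere does the plan say that efficacy will be claimed because iCBT changes and TAU does not. That stands too, and is why 26-41% is an illustration and not the plan's error rate. With gating on the interaction the figure is about 2.4%. The 54-versus-27 comparison also pools two groups that the model keeps apart.

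A condensed article may leave its full list of contrasts to an analysis plan that is not shown. This stands for what is absent, but not for what is present: the article does fix a contrast, and that contrast does not match the hypothesis. Even on the reading most favourable to the plan, as pre-post change compared between arms, the 2-month claim still has no contrast.

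Finally, a model with baseline as one of the responses gives a valid randomised comparison. Agreed: baseline adjustment is a gain in precision, not the correction of an error.

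**Conclusion.** The concern holds in a limited form. The plan tests iCBT against TAU at omnibus level, but the only follow-up contrasts it names run from pre- to post-treatment. No named contrast isolates the between-arm difference of H1 to H3 at post-treatment or, in particular, at 2 months. A significant omnibus result cannot fill the gap, since it could come from post-treatment only, from time alone, or from a difference between the two preference-chosen iCBT groups. The equality of power in step 3 rests on compound symmetry and pooled iCBT groups. The 26-41% figure rests on pooled groups, a fall of 0.3 to 0.4 SD, ρ of 0.5 to 0.7 and no gating, none of which the article states. This should be fixed before analysis because it concerns the primary hypothesis; it does not invalidate the planned model.

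**What to change.** In section 2.10.2, replace the sentence on pairwise contrasts with: *The treatment effect is the difference in mean HADS-T between iCBT (as randomised) and TAU at post-treatment and at 2-month follow-up, estimated from the LMM with baseline HADS-T as covariate (or baseline means constrained equal), with 95% CI, reported whatever the omnibus test shows; within-group pre-post changes are descriptive.* Use the same contrasts for the outcomes of H2 and H3, and state the time point of Hedges' g.

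The cost is one sentence and the matching contrast in the software. Baseline and 2-month scores are already collected in all groups, so neither data collection nor sample size changes.
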